### Randomization and allocation

The random sequence will be generated by an independent statistician from the Good Clinical Practice (GCP) Centre of Xiyuan Hospital of China Academy of Chinese Medical Sciences. Participants will be randomly allocated into either the treatment or placebo group, at a ratio of 1:1. Patients in the treatment group (*n* = 45) will receive the treatment of KBXG, while patients in the placebo group (*n* = 45) will receive placebo granules, that are identical in appearance to the KBXG. The KBXG and placebo with same packaging will be labeled according to the random number table. The random sequence will be kept in opaque sealed envelopes with consecutive numbers. These envelopes will be prepared by the GCP Centre. A rheumatologist will enroll participants. A research assistant will open the same numbered envelope based on the randomization enrollment number when an eligible participant can be included in the trial. Then, the research assistant will assign the drugs to the participant according to the sequence.

### Blinding

This is a double-blind trial in which patients, researchers, outcome assessors, and statistician are all blinded. Assignment of interventions will only be unblinded after database lock. Unblinding is permissible in emergency situations when researchers believe that it is necessary to perform any action for patient’s safety. The details of unblinding will be recorded.

### Data quality control

All researchers will receive professional training to understand the protocol. The researchers will obey to guidelines of GCP to ensure the safety, blinding and data quality. A specially trained researcher will carry out a quality control assessment every month to ensure the high-quality of this study.

### Data collection and management

Researchers are responsible for the collection of baseline information and trial data. The researchers will ensure that the study schedule is fully explained and participants are aware of the potential risks and benefits of the treatment before consent is obtained. Participants will receive phone calls before each visit to remind them of their time. Two independent investigators will double - checked all CRF. Data from the CRF will be inputted into the SPSS by the two data administrator. Once the trial is completed, we will perform a blind review to confirm the dataset. The final data will either be kept in a secure and lock-protected location.

### Statistical methods

Data analysis will be completed using SPSS 23.0, according to the intention-to-treat analysis and the per-protocol analysis. Baseline analyses will be performed using analysis of variance or non-parametric tests for continuous variables, and chi-squared or Fisher’s exact tests for categorical variables, respectively. Changes from baseline to post-treatment in DAS28-CRP, CDAI, TCM syndrome scores, VAS, average hands grip strength, HADS, L-BDM and US7 will be analyzed. The results of the two groups will be analyzed using analysis of covariance with associated 95% confidence intervals. The rates of participants achieving good responses on ACR will be compared. A two-sided *p* value of < or = 0.05 is considered statistically significant. Multiple imputations will be used to handle any missing data. For safety, the incidence of AEs will be analyzed and compared. The details of each AEs will be analyzed.

Participants with poor adherence, compliance of experimental drug <80%, or those no longer receiving medication and undergoing testing during the study will be included in the intention-to-treat analysis and excluded from the per-protocol analysis. Multiple imputation will be used for missing data.

### Data monitoring, harms and auditing

The Data Monitoring Committee (DMC) of Xiyuan Hospital of China Academy of Chinese Medical Sciences will meet once half a year to review trial conduct. The committee will conduct primary outcome interim analyses to oversee the safety and efficacy of the study when it reaches 50% of the recruitment. Besides, the committee will assess the status and quality of the study and make recommendations to continue or terminate the study. KBXG is relatively safe, and AEs are mild. Every patient could report any AEs to the researchers *via* phone and the researchers would immediately take action.

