### Sample size

The sample size is calculated based on the primary endpoint (the changes in DAS28-CRP). According to the previous exploratory clinical trial (unpublished), the effect size of the treatment group was 83.9%, with a power of 0.9 and alpha of 0.05, a total of 68 female patients should be included to determine an increase of 15% in disease activity improvement between the KBXG and placebo groups. To account for a 20% loss to follow-up, at least 85 female patients will be required in this trial. Thus, a total of 90 female patients (45 female patients in each group) are planned to be enrolled.

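### An efficacy interim on the primary outcome is paired with an unadjusted final 0.05, with no statement on stopping for benefit and no route for it under the blinding rule

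*Protocol article*

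**What the plan says.** Under Data monitoring, harms and auditing, the Protocol article states: "The committee will conduct primary outcome interim analyses to oversee the safety and efficacy of the study when it reaches 50% of the recruitment". The next sentence says that "the committee will assess the status and quality of the study and make recommendations to continue or terminate the study". The section gives no interim threshold and does not say whether a favourable result can end the trial or be reported as positive.

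Statistical methods sets a single criterion: "A two-sided *p* value of < or = 0.05 is considered statistically significant". Sample size uses the same level, "with a power of 0.9 and alpha of 0.05, a total of 68 female patients should be included", with no allowance for an earlier look.

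Blinding lists patients, researchers, outcome assessors and the statistician as blinded, and then says: "Assignment of interventions will only be unblinded after database lock". The one exception is an emergency affecting a patient's safety. The monitoring committee is not mentioned there.

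**The concern.** Each rule is ordinary by itself. Together they leave open whether the trial has one chance or two to declare benefit. With two chances, a final test at the full 0.05 no longer delivers a 5% error rate. A trial stopped for benefit on at most 22 or 23 patients per arm would also tend to overstate the effect, and the Discussion already concedes that the basis for the sample size may overestimate efficacy.

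Two further details are badly fixed. The look is triggered by recruitment, although treatment lasts 12 weeks, so the most recently enrolled patients will have no end-of-treatment value. And an efficacy review needs results by group, while the Blinding section authorises nobody to produce them before lock.

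**Working it through.** **Inputs from the Protocol article**
- Planned enrolment 90, allocated 1:1; 50% of recruitment is 45 patients (Sample size; Data monitoring).
- Two-sided 0.05; power 0.90; 68 patients before dropout; 20% loss (Sample size; Statistical methods).
- Treatment for 12 weeks (Trial design).

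**Assumptions.** One interim look, one endpoint, and Week 12 as the deciding visit. The article speaks of analyses in the plural and of two primary outcomes at every visit, so this is a simplification. The information fraction *t* is not given; values from 0.25 to 0.5 are shown.

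**Step 1: the plan's own level.** With one final test, 1 − P(|Z| < 1.96) = 0.05. The stated level is therefore correct if the interim cannot lead to a claim of benefit.

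**Step 2: two chances to claim benefit.** Let Z1 and Z2 be the interim and final statistics, with correlation √t under the null. Then

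overall α = 1 − P(|Z1| < c1, |Z2| < c2).

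For t = 0.5 the correlation is 0.707. With c1 = c2 = 1.96, both tests reject with probability 0.0169, so α = 0.05 + 0.05 − 0.0169 = 0.0831.

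| Interim rule, final test at 0.05 | t = 0.25 | t = 0.375 | t = 0.5 |
|---|---|---|---|
| No claim possible at the interim | 5.00% | 5.00% | 5.00% |
| Haybittle-Peto, p < 0.001 | 5.06% | 5.04% | 5.02% |
| O'Brien-Fleming value for t = 0.5, p < 0.0052 | 5.35% | 5.28% | 5.20% |
| p < 0.05 | 9.07% | 8.71% | 8.31% |

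A simulation of 4 million draws gave 8.31% at t = 0.5 and 9.08% at t = 0.25 for the last row.

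**Step 3: the trigger.** If all 45 recruited patients had Week 12 data, t would be 45/90 = 0.5 against a complete final data set. Anyone enrolled in the preceding 12 weeks lowers it. If about half of the 45 had reached Week 12, t would be about 22.5/90 = 0.25. The accrual rate is not given, so the shortfall cannot be fixed more closely.

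**Step 4: levels that restore 5%.** At t = 0.5 the O'Brien-Fleming boundary is p < 0.0052 at the interim (z = 2.797) and p < 0.0480 at the end (z = 1.977). The corresponding spending function gives 0.0031 and 0.0490. These values belong to t = 0.5. Using 0.0052 and 0.0480 unchanged at t = 0.25 gives 5.15%, and at t = 0.625 gives 4.92%.

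**Step 5: cost in power.** With the O'Brien-Fleming pair, 90% power becomes 89.8% at the same size. Holding 90% multiplies the size by 1.007: 68 × 1.007 = 68.5, so 69; 69/0.8 = 86.25, so 87, still within the planned 90.

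**The case against.** The strongest reply is that nothing in the text says the trial may stop for benefit. The sentence on termination opens with *Besides* and ties the recommendation to study status and quality, not to the efficacy result. A look used only for safety or futility does not raise the type I error. Nor does any sentence apply 0.05 at the interim; a boundary may stand in the full protocol, an analysis plan or a committee charter not shown here. All of this stands. A reader might infer that α is certainly inflated, to 8% or 9%. The documents do not support that: those figures are the worst case, and a strict boundary leaves an excess of a few tenths of a percentage point or less.

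A reader might also infer that the Blinding and Data monitoring sections flatly contradict each other. That goes too far. The committee is not among the blinded parties, and it could compare groups under neutral codes. What remains is that the listed statistician is blinded, unblinding before lock is reserved for emergencies, and no coded or closed route is described for the analysis that the other section requires.

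Finally, it is tempting to say that the look would use well under half the information. That depends on accrual speed, which is not stated.

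What the reply does not remove is the stated combination: an efficacy analysis of the primary outcome, a committee that may "make recommendations to continue or terminate the study", and an unadjusted final level. If an unseen boundary does allow a stop for benefit, a final 0.05 is still not exact.

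**Conclusion.** The point holds as a badly fixed combination of stated rules, with a conditional consequence. If benefit cannot be claimed and the trial cannot be stopped for it at the interim, type I error stays at 5%. If it can, the error per endpoint is above 5%: 5.02% to 5.20% at half the information for the two strict boundaries with a final 0.05, and at most 8.3% there, or 9.1% at a quarter of the information, if 0.05 serves at both looks. The range assumes one look and one endpoint. The Blinding and Data monitoring sections need to be reconciled on who may see results by group. All of this should be settled before any interim result is seen, because a rule chosen afterwards cannot restore the error rate.

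**What to change.** **Preferred.** State in Data monitoring that the half-way review covers safety and study conduct only, with no comparison of efficacy between groups and no stopping or claim for benefit. The final two-sided 0.05 then stands. State in Blinding how the committee receives any safety data by group. The cost is wording, plus giving up early stopping for benefit.

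**Alternative, if early stopping for benefit is wanted.**
- Trigger the look on a stated number of patients with Week 12 data, not on recruitment.
- Use an O'Brien-Fleming-type spending function evaluated at the information fraction actually reached; at exactly 50% the classical boundary is about 0.005 at the interim and 0.048 at the end. A trigger of 45 patients with Week 12 data would be 45/72 = 62.5% if 20% of the 90 are lost, so the 50% values should not be written in as fixed numbers.
- State how the boundary applies to both primary outcomes, DAS28-CRP and CDAI.
- Amend Blinding so that a statistician independent of the study team prepares a closed report for the committee, while the trial statistician stays blinded.

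The cost is a final level slightly below 0.05, about 0.2 percentage points of power at 50% information (90% to 89.8%), and an additional independent statistician.

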## Methods

### Trial design

This is a single-center, randomized, double-blind, parallel group, placebo-controlled clinical trial. The trial will be conducted in the Xiyuan Hospital of China Academy of Chinese Medical Sciences. A total of 90 eligible female participants will be randomized into the experimental group (KBXG) or the control group (placebo) with a 1:1 ratio. Two groups will continue their original treatment regimen during the trial. The duration of the intervention is 12 weeks, and follow-up is 12 weeks. Study visits will take place at baseline and at 4, 8, 12, 24 weeks. Every patient will be asked to visit within 3 days of the given time point. All participants will be required to sign the written informed consent before randomization. This protocol was compiled in line with the Standard Protocol Items: Recommendations for Interventional Trials (SPIRIT) Guidelines (Chan et al., 2013), which is presented in the Supplementary Material S1. The flowchart of this trial is presented in Figure 1.

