### Outcomes and measurements

#### Primary outcome

The primary outcomes are the change in DAS28-CRP and CDAI at every visit.

The DAS28-CRP is widely used as an indicator of RA disease activity and response to treatment, and clinical trials have used DAS28 to assess treatment effect (Gardiner et al., 2005; Jain et al., 2021; Zhang et al., 2022). A change of ≥1.2 score is considered clinically significant difference (Van Gestel et al., 1998). The DAS28-CRP is calculated as DAS28-CRP = 0.56*sqrt (TJC28) + 0.28*sqrt (SJC28) + 0.36*ln (CRP+1) + 0.014*VAS +0.96 (van Riel, 2014).

The CDAI is calculated as CDAI = TJC28 + SJC28 + overall disease activity on a 0–10 VAS completed by the patient + overall disease activity on a 0–10 VAS completed by the physician (Aletaha et al., 2005). High disease activity is defined as a CDAI >22, moderate activity as a CDAI >10 and ≤22, low activity as a CDAI >2.8 and ≤10, and remission as a CDAI ≤2.8.

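### The halfway look at efficacy on the primary outcome is not reconciled with the single unadjusted two-sided 0.05 level; if it can stop the trial at that level, the error rate is about 7–9%, not 5%

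*Protocol article*

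**What the plan says.** Four places in the Protocol article bear on this.

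- **Data monitoring, harms and auditing.** "The committee will conduct primary outcome interim analyses to oversee the safety and efficacy of the study when it reaches 50% of the recruitment". The next sentence lets the committee assess the status and quality of the study and "make recommendations to continue or terminate the study". No interim level, boundary or stopping criterion is given. The look is not described as limited to safety or futility.
- **Statistical methods.** One threshold is given: "A two-sided *p* value of < or = 0.05 is considered statistically significant".
- **Sample size.** The calculation is made "with a power of 0.9 and alpha of 0.05", with no allowance for an earlier test.
- **Blinding.** Patients, researchers, assessors and statistician are blinded, and allocation is revealed only after database lock, apart from emergencies. The interim analysis is not mentioned.

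**The concern.** An efficacy look at the primary outcome, by a body that may recommend termination, is normally paid for in the significance level. Here the design level and the final threshold are both the full 0.05. If the same threshold also governed the halfway look, a null treatment would have two chances to cross it, and the stated 5% would not hold even for one endpoint at one visit.

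The second consequence concerns the estimate. A trial that stops because a small interim sample has crossed a threshold reports, on average, an effect larger than the true one. The trial is meant to confirm efficacy, and the article's own limitations already accept that efficacy may have been overestimated in the planning. Neither problem can be repaired once unblinded interim results have been seen.

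**Working it through.** **Inputs from the Protocol article.** Two-sided level 0.05 (Statistical methods); alpha 0.05 and power 0.90 (Sample size); 90 patients allocated 1:1; one planned time point at 50% of recruitment, that is 45 patients or about 22 per arm; 12 weeks of treatment.

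**Assumptions.** Information fraction t at the look. When 45 patients have been recruited, at most half of the planned week-12 data can exist, and fewer if recent recruits have not reached week 12. I take t from 0.3 to 0.5. I also assume that the look is an unblinded comparison and that 0.05 is applied at it. The document states neither.

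**Step 1: the plan's own figure.** One final test at |Z| > 1.96 gives 0.0500. The stated 5% is reproduced when there is no interim test that can end the trial.

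**Step 2: two looks at 0.05.** Under no effect, Z1 (interim) and Z2 (final) are bivariate normal with correlation √t.

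- Either direction counts: error = P(|Z1| > 1.96 or |Z2| > 1.96).
- Only a result favouring KBXG can stop the trial, with a two-sided final test: error = P(Z1 > 1.96 or |Z2| > 1.96).

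| t | Either direction | Stop only in favour of KBXG |
|---|---|---|
| 0.5 | 8.31% | 6.66% |
| 0.4 | 8.63% | 6.82% |
| 0.3 | 8.93% | 6.97% |

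**Step 3: size of the estimate after an early stop.** With true effect θ and standard error SE at the look, let u = 1.96 − θ/SE. The mean estimate among looks that cross in favour of KBXG is θ + SE × φ(u)/(1 − Φ(u)).

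*Scaled to the power of the full trial.* θ/SE at the look is (1.96 + z_power) × √t.

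- 90% power, t = 0.5: (1.96 + 1.282) × 0.707 = 2.292. Mean estimate 1.26 times the truth.
- 80% power, t = 0.5: (1.96 + 0.842) × 0.707 = 1.981. Mean estimate 1.40 times.
- At t = 0.3 the same cases give 1.52 and 1.71 times.

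*Scaled in SD units at 22 per arm.* SE = √(2/22) = 0.302 SD, so the threshold is 1.96 × 0.302 = 0.59 SD (0.61 SD by t-test). The true effects below are assumptions and do not come from the document.

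- θ = 0.5 SD: mean estimate 0.80 SD, or 1.6 times.
- θ = 0.3 SD: mean estimate 0.75 SD, or 2.5 times.

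**Step 4: do standard boundaries repair it?** Overall error at t = 0.5, same bivariate normal:

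- Lan-DeMets O'Brien-Fleming, interim p ≤ 0.0031 (0.00305 unrounded) and final p ≤ 0.0490: 0.0500.
- Haybittle-Peto, interim p ≤ 0.001 and final p ≤ 0.05: 0.0502.

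**The case against.** A reader might infer that the plan commits to two unadjusted tests at 0.05 and so has an error rate of 8–9%. The document does not support that reading, for four reasons.

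- **Threshold.** The 0.05 rule stands in the description of the main analysis. The monitoring section gives no test and no p-value for the look.
- **Comparison.** The monitoring section does not say that the look compares the arms unblinded. Taken with the Blinding section, a pooled blinded review is possible, and that would spend no alpha.
- **Termination.** The sentence on continuing or terminating is separate from the one on the interim analysis, opens with a word that marks it as an addition, and concerns the status and quality of the study. An efficacy stop is a natural reading but not an explicit one. A committee that could stop only for harm or futility would not raise the false-positive rate.
- **Condensed source.** This is a journal article, and it says that a full protocol is available on request. A boundary may stand there, in an analysis plan or in a committee charter. Its absence here does not show that none exists.

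All four stand, and they make the figures conditional. They do not remove the point. The article goes beyond silence: it announces an efficacy look and also fixes the final level at 0.05. A spending boundary elsewhere would normally need a final level below 0.05, so the Statistical methods section would then be wrong as printed. The stated level stays essentially correct only with no efficacy stop or with a very strict interim level, and the article states neither.

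The 1.6 and 2.5 times figures should not be read as what this trial would produce. They rest on assumed effects; at the trial's stated 90% power and half information the figure is about 1.3.

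**Conclusion.** The point holds in conditional form. The article plans an interim efficacy look at the primary outcome by a committee that may recommend termination, fixes one 0.05 level without allowing for it, and does not reconcile it with the blinding rule.

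If the look is an unblinded comparison able to stop the trial for efficacy at the only stated threshold, and t lies between 0.5 and 0.3, the error rate for one endpoint is 8.3–8.9% (either direction) or 6.7–7.0% (stop only in favour of KBXG), against a stated 5%. At half information the reported effect after such a stop would average about 1.3 times the truth at 90% true power and 1.4 times at 80%, and more with smaller true effects or less information.

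The document does not show that an unadjusted efficacy stop is intended, or that no boundary exists. These figures concern one endpoint at one visit; having two primary outcomes is a separate matter.

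**What to change.** In the monitoring and Statistical methods sections, state one of the following.

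- **(a) No efficacy stop.** The interim is for safety and trial conduct only, and the final level stays at 0.05.
- **(b) A bounded efficacy stop.** Termination for efficacy may be recommended only beyond a boundary computed at the information actually available, not at the recruitment percentage. Examples: Lan-DeMets O'Brien-Fleming (p ≤ 0.0031 at 50% information, final p ≤ 0.0490), or Haybittle-Peto (p ≤ 0.001, final 0.05, overall 0.0502). The final level printed in Statistical methods must match the boundary chosen.

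In either case, amend the Blinding section to say whether the committee sees results by arm, who prepares them, and that everyone else stays blinded until database lock. If a boundary already exists in the full protocol, analysis plan or charter, cite it and align the stated final level.

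**Cost.** Wording only and no extra patients. The final level is at most 0.05 − 0.0490 = 0.001 stricter, and the chance of stopping early for efficacy is lower.

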### Ethics and dissemination

Protocol version: v3.0 was finished on 1 May 2021. This trial has been approved by the Ethics Committee of Xiyuan Hospital of China Academy of Chinese Medical Sciences (2021XLA014-3) and will be conducted under the supervision of the Ethics Committee. Any modifications to the protocol regarding trial design, eligibility criteria, sample sizes, or significant changes in the study will initially require agreement from the Ethics Committee. Participants will sign the informed consent forms at the baseline and their personal information will remain strictly confidential. Results will be published in a peer-reviewed academic journal. The full protocol, participant-level data, and statistical code are available from the corresponding author upon reasonable request.

